### Analysis

#### Qualitative study of feasibility and acceptability

Qualitative data obtained from semistructured interviews (conducted either by telephone or on virtual platforms for example, Microsoft Teams) with patients, carers and staff will be combined with documentary analysis (reports, meeting minutes) and will be used to inform within trial decision-making processes via a rapid feedback evaluation approach.^22^ Transcripts and key documents will be imported into NVivo and analysed using framework analysis.^23^ Data collection and analysis will be carried out in parallel and emerging findings will be shared with the trial team on a monthly basis to inform trial design and delivery.

The findings from the interviews and documentary analysis will be used to develop a discrete choice experiment to gain an understanding of preferences for trial participation and how participants trade-off different attributes of ^99m^TC-sestamibi SPECT/CT with other management scenarios. In addition, a survey will be conducted—informed by a rapid review of survey instruments reported in the published literature to capture the acceptability of interventions in clinical trials, to provide insights into the barriers or facilitators to patient decision-making and determine the degree of acceptability of ^99m^TC-sestamibi SPECT/CT.

#### Study of diagnostic accuracy

Diagnostic accuracy of ^99m^Tc-sestamibi SPECT/CT will be estimated by generating 2×2 tables for both avid and non-avid qualitative assessment, and relative radiotracer uptake ratio >0.6 and ≤0.6 for external validation of a predefined threshold from the literature.^24^ Analysis of a range of relative uptake ratios will be explored to assess performance at different thresholds. Diagnostic accuracy of ^99m^TC-sestamibi SPECT/CT will be calculated in terms of sensitivity, specificity and predictive values along with their 95% CIs. The prevalence of renal oncocytoma and other histology subtypes will be calculated with a 95% CI.

Inconclusive test results will be reported.^25^ The proportion of participants with invalid ^99m^TC-sestamibi SPECT/CT results, for example, due to technical failure, will be reported. The proportion of valid but inconclusive results will also be reported, and their impact on estimates will be assessed by including them as either test positive or test negative in sensitivity analyses. This is to inform how ^99m^Tc-sestamibi SPECT/CT might be used in the diagnostic pathway. If intended as a replacement test for histopathology, a valid but indeterminate ^99m^Tc-sestamibi SPECT/CT would be considered non-avid to avoid misclassifying malignant tumours as benign. If, however, ^99m^Tc-sestamibi SPECT/CT were to be used as a triage test, where avid tumours undergo confirmatory biopsy, then an indeterminate test could be considered avid to reduce the risk of surgery for benign pathology. The proportion of patients who do not complete the study schedule defined in the protocol will be calculated.

We will assess inter-rater and intrarater agreement using percentage agreement and Gwet’s first-order agreement coefficient.^26^

We do not anticipate the need to adjust for diagnostic drift for the reference test, given the short study duration. However, if current pathologic guidelines for renal neoplasia are updated during the course of the study archived samples will be rereviewed and reported according to the latest guidelines.

#### Study of health economics

Health economic modelling will be used to understand the potential cost-effectiveness of ^99m^TC-sestamibi SPECT/CT in the evaluation of patients presenting with an indeterminate renal mass.^27^ A decision analytic approach will compare the following scenarios:

Patients have empiric surgery (current standard-of-care).Patients undergo tumour biopsy, those consistent with cancer have surgery and those with benign histology have active surveillance.Patients undergo ^99m^Tc-sestamibi SPECT/CT, those with a ‘cold’ scan (suggestive of cancer) have surgery and those with a ‘hot’ scan (suggestive of benign tumour) have active surveillance.Patients undergo ^99m^Tc-sestamibi SPECT/CT, those with a ‘cold’ scan have surgery, and those with a ‘hot’ scan have a confirmatory biopsy (MIBI would be likened to a triage test to select patients for biopsy for tissue confirmation before embarking on active surveillance).

The model will be populated with evidence from trial and published literature.^28^ Where data are not available, an expert elicitation approach will be employed to provide parameter values.^29^ The analysis will then compare the different approaches to standard-of-care by estimating the incremental cost-effectiveness ratios and assessing the uncertainty of these estimates using value of information (VOI) analysis. The VOI analysis will quantify the potential value of further research, identify areas of study with the greatest potential benefit and generate recommendations on future study designs.

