### Eligibility criteria

Consecutive patients discussed at specialist multidisciplinary team meetings will be screened for eligibility over a planned 15-month recruitment period. The inclusion criteria for entry to the study are adult patients (≥18 years) of any gender with a clinical T1 indeterminate solid renal tumour (2–7 cm) on cross-sectional imaging, willing and able to provide informed consent. Patients will be required to have surgery or renal tumour biopsy planned as part of their standard clinical care. Patients entering watchful waiting or active surveillance pathways without histologic diagnosis will be excluded. Other exclusion criteria will include cystic tumours, pregnant and breastfeeding patients, those with a known allergy to ^99m^Tc-sestamibi and those unwilling or unable to undergo the study procedures.

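### The only ICER comparison the economic plan states is against empiric surgery, which does not rank biopsy, scan alone and scan then biopsy against each other

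*Protocol article*

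**What the plan says.** All the relevant text is in the protocol article, Study of health economics. It opens with "A decision analytic approach will compare the following scenarios" and lists four:

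1. "Patients have empiric surgery (current standard-of-care", the reference.
2. "Patients undergo tumour biopsy, those consistent with cancer have surgery and those with benign histology have active surveillance".
3. Scan alone, with surgery for cold scans, while "those with a ‘hot’ scan (suggestive of benign tumour) have active surveillance". This is the replacement role.
4. Scan as triage, where "those with a ‘cold’ scan have surgery, and those with a ‘hot’ scan have a confirmatory biopsy".

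It then states how the ICERs are formed: "The analysis will then compare the different approaches to standard-of-care by estimating the incremental cost-effectiveness ratios". The same sentence continues with "assessing the uncertainty of these estimates using value of information (VOI) analysis". The section names no other ICER comparator.

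The section on diagnostic accuracy separates the same two roles for the scan: indeterminate results are handled one way if it replaces histopathology and the other way if it selects patients for biopsy.

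**The concern.** A patient follows one of the four strategies, so the decision is which one to adopt. An ICER against a fixed baseline answers a narrower question: whether that strategy is acceptable compared with operating on everyone. Several strategies can pass that test together. One of them may still cost more and yield less than another (dominance), or may be beaten by a combination of two others (extended dominance). The ratios against surgery do not show either.

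Replacement versus triage is strategy 3 against strategy 4, and the value of either role also depends on biopsy, strategy 2. None of these contrasts is among the stated ratios. The section also intends the modelling to generate recommendations on future study designs, so a favourable ratio against a comparator that is easy to beat could carry an inefficient scan role forward.

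**Working it through.** The document gives no cost, QALY, ICER or threshold, so there is no planned figure to reproduce. The check asks whether the stated comparison can mislead. Thresholds of 20,000 and 30,000 per QALY are assumptions throughout.

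**Check 1: assumed increments against surgery (cost, QALY).** ICER = ΔC/ΔQ; net benefit = 20,000 × ΔQ − ΔC.

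| Example A | ΔC | ΔQ | ICER vs surgery | Net benefit at 20,000 |
|---|---|---|---|---|
| Biopsy | 300 | 0.050 | 6,000 | 700 |
| Scan alone | 500 | 0.040 | 12,500 | 300 |
| Scan then biopsy | 400 | 0.060 | 6,667 | 800 |

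Scan alone passes at 12,500, yet it costs more and yields less than both biopsy and scan then biopsy.

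Example B: biopsy (300, 0.050), scan alone (900, 0.060), scan then biopsy (1,000, 0.055). Against surgery the scan strategies show 15,000 and 18,182, both below 20,000. Scan alone against biopsy is (900 − 300)/(0.060 − 0.050) = 60,000, and scan then biopsy is dominated by scan alone. In both examples, net benefit ranks the strategies in the same order at 30,000.

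**Check 2: a small decision tree.** From the protocol article: 30% benign (stated as an upper figure), scan sensitivity 0.92 and specificity 0.88, biopsy non-diagnostic 15%. Assumed: biopsy sensitivity 0.95 and specificity 0.98 for benign disease, with non-diagnostic cases going to surgery; costs of surgery 8,000, surveillance 2,500, biopsy 900, scan 500; QALY losses of surgery 0.05, biopsy 0.002, and missed cancer L.

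Probability of surveillance:
- Biopsy: 0.85 × (0.3 × 0.95 + 0.7 × 0.02) = 0.2542.
- Scan alone: 0.3 × 0.92 + 0.7 × 0.12 = 0.276 + 0.084 = 0.36.
- Scan then biopsy: 0.85 × (0.276 × 0.95 + 0.084 × 0.02) = 0.2243.

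Cost = 8,000 − 5,500 × P(surveillance) + test costs, where scan then biopsy pays 500 + 0.36 × 900. QALY = −0.05 × P(surgery) − biopsy loss − L × P(missed cancer), with P(missed cancer) of 0.85 × 0.014 = 0.0119 for biopsy, 0.084 for scan alone, and 0.85 × 0.00168 = 0.001428 for scan then biopsy.

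At L = 0.15:

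| Strategy | Cost | QALY | Difference from surgery |
|---|---|---|---|
| Surgery | 8,000 | −0.0500 | – |
| Biopsy | 7,502 | −0.0411 | −498, +0.0089 |
| Scan alone | 6,520 | −0.0446 | −1,480, +0.0054 |
| Scan then biopsy | 7,590 | −0.0397 | −410, +0.0103 |

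All three alternatives dominate surgery. In the incremental ranking, biopsy against scan alone is about 279,000 per QALY and scan then biopsy against biopsy about 65,000, so biopsy is extendedly dominated. Scan then biopsy against scan alone is 1,070/0.00488, about 219,000.

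**Sensitivity to L.** For scan then biopsy against scan alone, ΔC = 1,070 and ΔQ = −0.0075 + 0.0826 × L.

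| L | ΔQ | Result |
|---|---|---|
| about 0.09 or less | zero or negative | dominated by scan alone |
| 0.15 | 0.0049 | about 219,000 |
| 0.60 | 0.0420 | about 25,500 |
| 0.80 | 0.0586 | about 18,300 |

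At L = 0.09, scan then biopsy still dominates surgery (−410, +0.0104) while scan alone dominates it. At 0.80 it has the highest net benefit at both thresholds. Scan alone dominates surgery only while 0.05 × 0.36 exceeds 0.084 × L, that is, for L below about 0.21; at 0.60 and 0.80 it is cheaper but loses QALYs against surgery.

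**The case against.** Several points on the other side stand.

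- The text does not say that comparison with surgery is the only one. It opens by saying the four scenarios will be compared, and it excludes neither dominance nor net benefit. A reader might infer that the investigators have ruled out a full ranking. The article does not support that; it supports only that no other ICER comparator is stated.
- This is a condensed article, and the full protocol or a health economics plan may specify an incremental analysis. Absence of detail would be no finding. The point rests instead on the method that the article does state.
- Value of information computed from the expected net benefit of all four strategies would reveal the best one. The article does not say that it will be run pairwise. Nor does it say that it will be four-way, and it attaches the method to the ICER estimates.
- A table of cost and QALY differences from surgery contains what is needed to rank all four by subtraction. That is so, but the plan states ratios, and the ratios alone do not.
- The illustration is fragile. It turns on the assumed loss for a missed cancer. It applies accuracy figures for oncocytoma against other lesions to all benign tumours, and it charges the same loss to every avid cancer although the Introduction describes that subset as generally indolent. A reader might infer from the 219,000 figure that triage is poor value. It does not show that.

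A reader might also infer that labelling surgery as standard-of-care is wrong, because Eligibility criteria says "Patients will be required to have surgery or renal tumour biopsy planned as part of their standard clinical care". That does not follow. That sentence is an entry rule that requires planned surgery or biopsy, while the Introduction reports limited adoption of biopsy and says most patients with an incidental mass are treated for presumed cancer. The label is consistent with this.

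**Conclusion.** The point holds in a limited form. The only ICER comparison stated is against empiric surgery, and such ratios do not rank biopsy, scan alone and scan then biopsy among themselves. A dominated or extendedly dominated scan strategy could therefore be reported as cost-effective, and the stated ratios would not answer the replacement-versus-triage question.

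The logic does not depend on any particular inputs, but the size of the problem does. In the assumed tree, the contrast between the two scan roles runs from dominated to about 18,300 per QALY as the missed-cancer loss moves from about 0.09 to 0.80. Whether the eventual conclusion would change cannot be known from the document.

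Severity is low to moderate: this is early modelling in a feasibility study whose primary outcome is recruitment rate, and the wording can be corrected before the analysis is done.

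**What to change.** Replace the ICER sentence with a fully incremental analysis. Rank the four strategies by expected cost, remove those that are dominated or extendedly dominated, and report each remaining ICER against the next less costly non-dominated strategy. Report expected net benefit for all four at the chosen thresholds, and state that the value of information analysis is based on the four-way decision. Keep the comparison with empiric surgery as a secondary display. If a fuller plan already specifies this, bring the published sentence into line with it.

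The cost is one or two sentences and slightly more reporting, with the same model and inputs and no new data. The headline ICERs may look less favourable than those against surgery alone.

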### Data collection

Case report forms (CRFs) in paper and electronic format will be trialled. The CRFs will not bear the participant’s name or other directly identifiable data. The participants’ study ID will be used for identification purposes. Study-related procedures will be carried out during the baseline routine clinical visit, ^99m^Tc-sestamibi SPECT/CT visit and thereafter by telephone or email according to participant preference, as shown in table 1. CCRFs will be checked for completeness and accuracy by designated individuals against source data. Study data captured in paper format will be transcribed to an electronic database. Quality of life data will be captured using the previously validated EQ-5D-5L instrument.^30^ No analysis will begin until accuracy of the data has been assured. The final trial data set will be accessible to the chief investigator, statistician and health economist.

**Table 1 T1:** Visit schedule and assessments

Procedures	Screening	Baseline	Intervention	24–72 hour follow-up	Follow-up (standard of care)	Interview follow-up
Demographics		X				
Medical history	X	X				
Consent (obtained by clinician/research nurse)		X				
Imaging	X					
^99m^Tc-sestamibi SPECT/CT			X			
QoL questionnaire		X		X		
Adverse event reporting			X	X		
Histology test and result					X	
Semi-structured interview						X

SPECT: Single photon emission computed tomography.

QoL: Quality of life.

A participant may withdraw their consent to participate at any time prior to the ^99m^Tc-sestamibi SPECT/CT scan. The decision to withdraw will be recorded in the CRF and medical notes. Participants withdrawing prior to ^99m^Tc-sestamibi SPECT/CT will be replaced. If following ^99m^Tc-sestamibi SPECT/CT, the participant states they do not wish to participate in scheduled follow-up (EQ-5D-5L completion), or deviate from the protocol, then data already collected will be kept and analysed. These patients will not be replaced.

Baseline data items will include the following:

Baseline demographics (age, gender, ethnicity, medical and surgical history, current medication and allergies).Baseline blood test results (full blood count, renal function, coagulation screen).Baseline imaging (multiphase (to include non-contrast, arterial-phase, venous-phase and delayed-phase), contrast-enhanced CT or MRI of the abdomen).Renal tumour characteristics (complexity scoring, location, number of lesions).Quality of life questionnaire (EQ-5D-5L).

The following data on resource use will be collected at the time of the intervention

Duration of visit to nuclear medicine department.Adverse events (AEs) during and immediately post-MIBI-kidney.

The following data will be collected at postintervention follow-up by telephone or email

AEs following MIBI-kidney.Quality of life questionnaire (EQ-5D-5L).

After participation in the trial participants will continue follow-up as per standard care.

### Patient and public involvement

Patient and public involvement (PPI) has been central to the project concept and design. A prestudy PPI focus group informed the trial protocol and plain English summary. An online PPI survey received 231 responses and indicated 90% would be willing to participate in the proposed study. In addition to the qualitative workstream, PPI representatives from Kidney Cancer UK will form a study support group, meeting at regular intervals throughout the trial to provide advice and input on any trial challenges and developing/approving dissemination materials.

### Harms

^99m^Tc-Sestamibi has been used for cardiac and parathyroid imaging globally for decades and is known to be a safe radiopharmaceutical. The radiation exposure from one MIBI-kidney scan is 14 mSv, equivalent to approximately 5 years of average UK background radiation.^31^ As MIBI-kidney is the only study intervention in addition to standard care, a data-monitoring committee will not be required.

All AEs, whether related or unrelated to MIBI-kidney, will be documented in the patient’s notes, study CRF and the AE log. The AE log will be sent to the Sponsor (University College London & University College London Hospitals Joint Research Office) at least once per year. Incidental clinically significant abnormalities identified on MIBI-kidney will be recorded as AEs and communicated to the referring clinician and patient. All serious AEs will be recorded on an SAE form and reported to the Sponsor and relevant REC within 15 working days of the chief investigator becoming aware of the event.

### Auditing

Investigators and sites will permit trial-related monitoring, audit, REC review and regulatory inspection(s) and provide access to required data and documents.

### Ethics and dissemination

Ethical approval for this study has been granted (UK HRA REC 20/YH/0279). Protocol amendments will be promptly disseminated to Sponsor, investigators and trial steering committee members. The study is recorded on the trial registration website. The trial involves the administration of unsealed radioactive substances. An Administration of Radioactive Substances Advisory Committee certificate has been granted (AA-3990).

Study outputs will be presented at national and international conferences and published in peer-reviewed journals. Patient representatives will be involved in output dissemination to the public individual trial participants via study newsletter.
